## Abstract

**Background:**

The proposed trial is to examine the feasibility of prostate-specific membrane antigen (PSMA) positron emission tomography/computed tomography (PET/CT)-guided cytoreduction plus apalutamide and androgen deprivation therapy (ADT) for newly diagnosed metastatic hormone-sensitive prostate cancer (mHSPC) at oligometastatic state.

**Methods:**

CHAMPION (NCT05717582) is an open-label, single-arm, phase II trial, planning to enroll newly diagnosed mHSPC cases with oligometastases (≤ 10 distant metastatic sites in conventional imaging). Patients will receive 6 cycles of apalutamide plus ADT. Patients with oligometastatic disease at PSMA PET/CT after 3 treatment cycles will receive cytoreductive radical prostatectomy. PSMA PET/CT-guided metastasis-directed external radiation therapy will be determined by the investigators. Apalutamide plus ADT will be continued for 2 weeks postoperatively. The primary endpoint is the proportion of patients with undetectable prostate-specific antigen (PSA), no disease progression, and no symptom deterioration after 6 cycles of apalutamide plus ADT. Secondary endpoints include the percentage of patients with PSA ≤ 0.2 ng/mL and oligometastases by the end of 3 treatment cycles, PSA response rate, and safety. Fleming’s two-stage group sequential design will be adopted in the study, where the null hypothesis is that the rate of patients with an undetectable PSA is ≤ 40% after 6 cycles of treatment, while the alternate hypothesis is an undetectable PSA of > 60%; with one-sided α = 0.05, power = 0.80, and an assumed dropout rate of 10%, the required number of patients for an effective analysis is 47. Enrolment in the study commenced in May 2023.

**Discussion:**

The multi-modal therapy based on treatment response may improve the prognosis of newly diagnosed mHSPC patients with oligometastases.

**Trial registration:**

The study is registered with Clinical Trials.Gov (NCT05717582). Registered on 8th February 2023.

**Supplementary Information:**

The online version contains supplementary material available at 10.1186/s12885-024-12395-3.

## Introduction

Prostate cancer is a lethal disease especially when progressing into a metastatic status [1, 2]. The proportion of patients with newly diagnosed prostate cancer at advanced stages is higher in China than in Western countries, and most patients have distant metastases diagnosis [3]. Currently, novel hormone therapy (NHT) plus androgen deprivation therapy (ADT) has become the standard first-line treatment for patients with metastatic hormone-sensitive prostate cancer (mHSPC) [4]. However, the 5-year overall survival (OS) for patients receiving this regime remained unsatisfying [5]. Treatment strategies should be refined to improve the prognosis of mHSPC.

Oligometastatic prostate cancer is an intermediate phase between a primary localized state and an extensive metastatic state and differs from widely metastatic lesions. The dynamic response to therapeutic treatment emphasizes the importance of this treatment window to defer disease progression [6, 7]. The definition of oligometastatic disease is ambiguous in prostate cancer with less than 3, 5, or 10 metastatic sites and free of visceral metastasis [8–15]. A phase II clinical trial demonstrated that the addition of local treatment (mostly cytoreductive radical prostatectomy [cRP], accounting for 85%) to systemic therapy significantly prolonged radiographic progression-free survival (rPFS) and OS in mHSPC patients with ≤ 5 metastases [16]. Recent evidence has showed survival benefits and cost-effectiveness for multi-modal therapy (MMT) in mHSPC patients with limited metastatic lesions [17, 18]. Besides systemic therapy, MMT strategy further included local treatment (e.g., cRP and external beam radiotherapy for prostate) and metastasis-directed therapy (MDT, e.g., stereotactic body radiation therapy [SBRT]) [19–21]. However, current MMT evidence mostly include traditional ADT instead of NHT. The benefit of NHT in MMT strategy should be further evaluated.

Prostate-specific membrane antigen (PSMA) positron emission tomography/computed tomography (PET/CT) has displayed diagnostic accuracy in prostate cancer [22]. Although, more metastatic lesions could be identified by PSMA PET/CT, the migration from low- to high-volume disease only occurred in 22% of patients according to the CHAARTED criteria [23]. Therefore, the value of PSMA PET/CT for newly diagnosed mHSPC still needs to be evaluated by its application during natural disease course. In a prospective trial, about 63% of newly diagnosed oligometastatic prostate cancer cases had a complete radiological response to systemic therapy plus pelvic lymph node dissection [PLMD] guided by PSMA PET/CT and 47% of cases had a pathological complete response, suggesting the potential value of PSMA PET/CT in treatment evaluation and decision-making [24]. Furthermore, a previous study by our group found that about 50% of nonmetastatic castration-resistant prostate cancer on conventional imaging has been proved to be metastatic on PSMA PET/CT, and the incidence of metastatic disease was less frequent in patients who received SBRT compared with those who did not [25].

These results suggested that when systemic therapy had inhibited the function of most distant metastases, the functional residual lesions might need individualized MDT. MMT strategies based on treatment response evaluated by PSMA PET/CT might be optimal for managing mHSPC with oligometastatic state.

### Trial overview

This study is a prospective, single-arm, open-labeled, phase II clinical trial that will be conducted from March 2023 to December 2024 at Fudan University Shanghai Cancer Center (FUSCC). Patients with newly diagnosed metastatic mHSPC and ≤ 10 distant metastatic sites will be enrolled for the study. The patients will receive 6 cycles of apalutamide in combination with ADT. Gallium-68 (^68^Ga) or fluorine-18 (^18^F) PSMA PET/CT will be used for viewing metastatic sites after 3 treatment cycles. In patients with metastatic oligoresidues (≤ 10 distant metastases), cRP will be performed. During prostatectomy, ADT will be maintained. Apalutamide plus ADT will be continued for 2 weeks after surgery, and PSMA PET/CT-guided metastasis-directed SBRT will be adopted as determined by the investigators (Fig. 1). This study protocol will follow the Good Clinical Practice standards and the Declaration of Helsinki principles. This prospective study has been approved by the Clinical Research Ethics Committee of FUSCC (number 1909207–12) and has been registered with ClinicalTrials.gov (NCT05188911). The written informed consent will be obtained from all participants.

**Fig. 1 Fig1:**
[figure not shown]
The flowchart of the proposed trial. MDT: metastasis-directed therapy; cRP: cytoreductive radical prostatectomy; ECOG PS: Eastern Cooperative Oncology Group Performance Status; RT: radiation therapy; ADT: androgen deprivation therapy; PSMA-PET/CT: prostate-specific membrane antigen positron emission tomography/computed tomography; PSA: prostate-specific antigen; CTCAE: Common Terminology Criteria for Adverse Events

The primary endpoint is the proportion of patients with undetectable prostate-specific antigen (PSA), no disease progression, and no symptomatic deterioration after 6 treatment cycles. Undetectable PSA is defined as ≤ 0.2 ng/mL and confirmed by two successive evaluations at least 3 weeks apart. Disease progression will be evaluated by a blinded independent central review (ICR) according to the Response Evaluation Criteria in Solid Tumours (RECIST) version 1.1. Symptomatic deterioration is referred to as a situation where the treatment needs to be interrupted, but with no apparent disease progression.

The secondary endpoints include the following:Percentage of cases with undetectable PSA after 3 treatment cycles.PSA50 and PSA90 response rate after 3 and 6 treatment cycles. PSA50 and PSA 90 response rate are the percentages of patients who have a reduction of greater than 50% and 90% from baseline, respectively.Comparisons of baseline conventional imaging and PSMA PET/CT imaging features, including tumor-node-metastasis (TNM) staging, molecular imaging TNM (miTNM) classification, number of metastases, and metastatic sites.Proportion of patients with ≤ 10 metastases (except pelvic lymph node metastases without new metastases) assessed by PSMA PET/CT at the end of cycle 3.Comparison of conventional imaging and PSMA PET/CT imaging features at the end of the 3 and 6 treatment cycles, including change in prostate volume, number and volume of prostate tumor nodules, distribution of metastatic lesions and number of metastatic lesions.Safety assessment: including adverse events (graded according to National Cancer Institute's Common Terminology Criteria for Adverse Events 5.0 criteria) and surgical complications (graded according to Clavien-Dindo classification).Assess the feasibility of implementing cRP ± MDT based on the number of metastases in PSMA PET/CT.

The exploratory endpoints include the following:SUVmax and tumor volume in PSMA PET/CT after 3 treatment cycles, and their correlations to PSA response rate and demographic characteristics.Subgroup analysis stratified by baseline SUVmax and number of metastases.Pathological complete response (defined as the percentage of patients having no surviving tumor cells in prostatectomy specimens following preoperative treatment), minimal residual disease (defined as residual tumor ≤ 5 mm in prostatectomy specimens following preoperative treatment), and pathological tumor-node.Time to PSA progression, defined as the time from the beginning of treatment to the first PSA progression based on Prostate Cancer Working Group 2 criteria.rPFS, defined as the time from treatment initiation until radiographic progression based on RECIST 1.1 criteria and death from any cause.Metastatic progression pattern in patients achieving a minimal residual state after treatment.Natural course of disease in patients with multiple metastases before and after treatment.Biomarker search: prostate cancer-related molecular markers.

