
### Study treatment

Patients will receive apalutamide in combination with ADT. Each treatment cycle will be 28 days, with a total of 6 treatment cycles. Apalutamide will be given orally at a dosage of 240 mg once daily, but this dose will be adjusted according to the instruction in case of intolerability [26]. The ADT regimen consists of a gonadotropin-releasing hormone analog (GnRHa), either a GnRHa agonist or a GnRHa antagonist. The type, frequency, and dosage of the ADT will be determined by the investigators, and the dosage will be adjusted according to the instruction if adverse events occur.

The PSMA PET/CT imaging will be performed in a 2-week window after 3 cycles of apalutamide plus ADT. Based on the PSMA PET/CT images, the investigators will decide on subsequent cytoreduction. The patients with ≤ 10 distant metastatic sites by PSMA PET/CT, will be treated with cRP with/without MDT. cRP and PLND will be performed based on the evaluation of preoperative PSMA PET/CT images. ADT will be maintained during the whole perioperative period, while apalutamide will be discontinued for at least 1 week before the day of surgery. Apalutamide plus ADT will be restored 2 weeks postoperatively based on the evaluation by investigators. A multidisciplinary team including investigators will reach a decision on the application of MDT. SBRT will be performed and the dosages for different body sites will vary based on the tolerance level of the organ with metastases and the surrounding normal tissue. The lesions will be exposed to radiation with a recommended protocol using guidelines and the clinical experience of the investigators. The patients will be concurrently administered apalutamide plus ADT during the radiotherapy. For patients undergoing cytoreduction (cRP with/without MDT), the entire treatment duration will not exceed 8 months.

Cases recovering from the oligometastatic state after three cycles of apalutamide plus ADT assessed by PSMA PET/CT imaging will continue to receive apalutamide plus ADT. Treatment will be terminated if the patients cannot benefit from the therapy, experience intolerant toxicity, or withdraw the informed consent. For patients who discontinue apalutamide treatment plus ADT within the first three months of the trial, subsequent treatment will be determined by the investigators.

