### Assessments

Serum PSA will be assessed, and PSMA PET/CT imaging will be performed once every 3 cycles during the systemic treatment [27]. If serum PSA level increases or patients suffer from osteodynia, chest, abdominal, and pelvic CT/MRI imaging will be performed. The participants will be followed up via telephone until the end of the study, death, or loss to follow-up, within ± 4 weeks (Table 1). ^68^Ga or ^18^F can be used as a tracer and the type of tracer for each patient will remain unchanged throughout the study.

**Table 1 Tab1:** Participant timeline

	Screening Period		Observation and Treatment Period											Group Exit Confirmation	Follow-up Period
Item	Within 14 days before first dosing	Within 7 days before first dosing	1st cycle	2nd cycle	3rd cycle		Planned surgery date (First 7 ± 1 days)	Surgery date	After surgery date (14 ± 3 days)	4th cycle	5th cycle	6th cycle	6th cycle	Group-exit investigation & observation confirmation	Safety & survival follow-up
			C1D1 (± 3 days)	C2D1 (± 3 days)	C3D1 (± 3 days)	C3D28 (± 3 days)				C4D1 (± 3 days)	C5D1 (± 3 days)	C6D1 (± 3 days)	C6D28 (± 3 days)	C6D28 + 30 (± 7 days)	Once every 3 m in 1st–2nd y; once every 6 m in 3rd y
Signing of informed consent [1]	√														
Demographic characteristics and history of tumor or other diseases [2]	√														
Vital signs [3]		√				√	√						√	√	
Physical examination [4]		√													
ECOG scoring [5]		√				√							√	√	
Testosterone examination [6]	√														√
Blood routine [7]		√													
Urine routine [8]		√													
Occult blood in stool [9]		√													
Blood biochemistry [10]		√													
Blood coagulation function [11]		√													
HIV, Hepatitis B, Hepatitis C [12]	√														
12-lead electrocardiogram [13]		√													
Ultrasonic cardiogram [14]	√														
Prostate specimen examination [15]	√							√							
PSA examination [16]		√				√							√	√	√
Imaging examination [17]	√												√		√
Bone scan [18]													√		√
PSMA-PET [19]	√					√									√
Metastasis-directed therapy [20]										√					
Systemic therapy drug compliance [21]						√							√	√	
Concomitant drug/therapy [22]	√													√	
Adverse event recording [23]						√							√	√	
Progressing event, survival state, and subsequent tumor treatment [24]														√	√

Description:

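### The cycle-3 undetectable-PSA endpoint carries a two-reading confirmation whose only scheduled second reading is C6D28, so as defined it does not isolate response to three cycles of systemic therapy

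*Protocol article*

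**What the plan says.** **Definition.** In the Trial overview section (text after Fig. 1), PSA is undetectable if it is at most 0.2 ng/mL and "confirmed by two successive evaluations at least 3 weeks apart". The sentence stands in the primary-endpoint paragraph. The list of secondary endpoints that follows opens with "Percentage of cases with undetectable PSA after 3 treatment cycles". It uses the same term and gives no definition of its own.

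**Abstract.** The Methods part of the abstract describes a cycle-3 secondary endpoint as the percentage of patients with PSA at or below 0.2 ng/mL and "oligometastases by the end of 3 treatment cycles, PSA response rate, and safety". It mentions no confirmation. It joins the PSA threshold with oligometastases, whereas the Trial overview lists undetectable PSA and the metastasis count at cycle 3 as two separate endpoints.

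**Schedule.** The Assessments section says: "Serum PSA will be assessed, and PSMA PET/CT imaging will be performed once every 3 cycles during the systemic treatment". The PSA row of Table 1 is ticked at screening (within 7 days before first dosing), C3D28, C6D28, group exit (C6D28 + 30, ± 7 days) and follow-up. It has no tick at C1D1, C2D1, C3D1, the three surgery columns, C4D1, C5D1 or C6D1.

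**Treatment between the two PSA visits.** Under Study treatment, "Each treatment cycle will be 28 days, with a total of 6 treatment cycles". After the cycle-3 PSMA PET/CT, patients with at most 10 distant sites "will be treated with cRP with/without MDT". After surgery, "Apalutamide plus ADT will be restored 2 weeks postoperatively based on the evaluation by investigators".

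**The concern.** C3D28 is the last scheduled PSA before cytoreduction. A cycle-3 PSA rate is therefore the natural summary of what apalutamide plus ADT achieves before surgery and radiotherapy are added. If the confirming value comes only at C6D28, a patient's cycle-3 status is settled by a measurement that already reflects three further cycles and, in operated patients, removal of the prostate. A patient with a low PSA at C3D28 whose PSA has risen by C6D28, or who has no value there, would be classed as not having responded at cycle 3.

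An analyst could instead apply the single-value wording of the abstract. The two rules can give different rates from the same data, and the article does not say which applies.

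**Working it through.** The plan gives no figure for the confirmation interval, so there is none to reproduce. The check sets the definition against the schedule.

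**Inputs**
- Required spacing: at least 3 weeks = 21 days (Trial overview).
- Cycle length: 28 days (Study treatment).
- PSA visits and windows: Table 1, PSA row read column by column against the header (16 columns in each).

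**Step 1: place the PSA visits on a day scale, with C1D1 as day 1**

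| PSA visit | Treatment day | Window |
|---|---|---|
| Screening | before first dose | within 7 days |
| C3D28 | 3 × 28 = 84 | ± 3 |
| C6D28, no surgical gap | 6 × 28 = 168 | ± 3 |
| Exit | 168 + 30 = 198 | ± 7 |

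**Step 2: find a partner for C3D28**
- Preceding value: screening, taken before treatment. It cannot show response to treatment.
- Next value: C6D28. Nominal gap 168 − 84 = 84 days. With both ± 3-day windows the range is 84 − 6 = 78 to 84 + 6 = 90 days.

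C6D28 formally satisfies a minimum of 21 days, because the definition sets no maximum. It is also the only scheduled value that can serve.

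**Step 3: operated patients**

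Table 1 puts the surgery columns between C3D28 and C4D1, so the gap is longer than 84 days. How much longer is not fixed. As an illustration only, adding 7 pre-operative and 14 post-operative days in sequence gives 84 + 7 + 14 = 105 days. The 8-month limit on treatment gives an upper bound: 8 × 30.44 − 84 ≈ 160 days, if the limit runs from first dose. The conclusion needs neither figure.

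**Step 4: effect on the estimate**

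Let r be the proportion with C3D28 PSA at or below 0.2 ng/mL, and q the proportion of those who are also at or below 0.2 ng/mL at C6D28.
- Single-value rate: r.
- Rate under the printed definition: r × q.
- Difference: r × (1 − q).

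The article gives neither r nor q, so the difference cannot be sized. But q is determined wholly by what happens after cycle 3.

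**Step 5: the primary endpoint for comparison**

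C6D28 has a nearby partner, the exit visit, nominally 30 days later. If exit is timed from the actual C6D28 draw, the smallest gap is 30 − 7 = 23 days, above 21. The definition and the schedule therefore fit each other at cycle 6 but not at cycle 3.

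**The case against.** **Table 1 may not list every blood draw.** Coagulation is ticked only at screening, yet the table notes also place it at the end of treatment. Adverse events are ticked at three visits but recorded continuously. The PSA row carries a note number, while the printed notes are lettered and none describes PSA sampling. A fuller protocol could contain interim PSA tests. This lowers certainty, but nothing in the article plans such a test.

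**The sentence in Assessments is ambiguous.** The three-cycle frequency may belong to the imaging alone, and the next sentence presupposes some PSA monitoring. That is fair. The finding therefore rests on the PSA row of Table 1, with which the sentence is compatible.

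**Confirmation may be meant for the primary endpoint only.** Its position in the primary-endpoint paragraph and the wording of the abstract both suggest so. This is probably the intention, and the fix adopts it. As printed, though, the secondary endpoint reuses the defined term without exemption.

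**The endpoint is descriptive.** No test, stopping rule or sample size uses it, and cytoreduction depends on the PSMA PET/CT site count. This stands and limits the importance of the point.

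**Stronger readings that the documents do not support**
- A reader might infer that the cycle-3 rate must be 0%, since no confirming value precedes surgery. The definition does not require confirmation before surgery and sets no upper limit on spacing, so C6D28 can formally confirm.
- A reader might infer that the primary endpoint can miss the 21-day rule, since 30 − 7 − 3 = 20. This needs exit timed from the nominal date, which the article does not say, and both windows at opposite extremes.
- A reader might add the 2-week PET window to the surgical intervals (84 + 14 + 7 + 14 = 119 days). Those intervals may overlap, so the sum is not a reliable estimate.

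**Conclusion.** The point holds for the cycle-3 secondary endpoint. With the printed definition and schedule, confirmation of a C3D28 value comes nominally 84 days later (78 to 90) without surgery and later still with it. The resulting rate depends on cycles 4 to 6 in all patients who continue and, in those operated on, also on prostatectomy with or without metastasis-directed therapy. It is obtainable, but it is not a measure of response to three cycles of systemic therapy before cytoreduction.

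This rests on two assumptions: that Table 1 shows all planned PSA visits, and that the defined term carries its confirmation rule into the secondary endpoint. The effect on the reported rate cannot be quantified from the article. The primary endpoint has a workable confirming visit, and the design does not depend on the point. It is worth correcting before analysis because a secondary result would otherwise rest on an unintended rule and the correction is close to free.

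**What to change.** 1. Define the cycle-3 endpoint as PSA at or below 0.2 ng/mL on the single C3D28 value, without confirmation.
2. Limit the two-evaluation rule to the primary endpoint and name the pair: C6D28 first, exit visit second.
3. Reconcile the abstract with the Trial overview by stating whether the cycle-3 PSA threshold and the metastasis count are one combined endpoint or two. The abstract supports an unconfirmed threshold but does not match the body exactly.

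**Cost.** Only wording changes; no visit is added. The cycle-3 rate is then unconfirmed and may be slightly higher than a confirmed one, which the report should say. The sample size and decision rule stay as they are. So does the primary-endpoint result, provided the exit value is already the intended confirmation.

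**Alternative if a confirmed cycle-3 rate is wanted.** Add a PSA at C3D1 and state that C3D1 and C3D28 form the pair. The nominal gap is 84 − 57 = 27 days, and 27 − 3 − 3 = 21 at the window limits, so it just meets the rule. It costs one blood draw per patient and is stricter, because PSA must already be low at the start of cycle 3.

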## Participants and methods

This study will enroll patients with newly diagnosed mHSPC and distant metastases of ≤ 10 detected by conventional imaging. All patients will receive apalutamide plus ADT.

